### Patient and public involvement

The proposed protocol has been informed, revised, and refined in consultation with stroke patients.

### Ethics and dissemination

The study was approved by New York University’s Institutional Review Board (FY2024–8826) and was registered on ClinicalTrials.gov (NCT07127159). The study follows the recommendations of the NIH Music-Based Intervention Toolkit (Edwards et al., 2023) and of SPIRIT (Standard Protocol Items: Recommendations for Interventional Trials; Chan et al., 2013). All participants will provide written informed consent prior to enrollment. Compensation will be provided for each completed evaluation session, and transportation costs will be covered as needed. As part of ethical approval, this protocol includes a Data and Safety Monitoring Plan (DSMP) and an independent monitoring committee (IMC). The IMC is composed of three members who are not involved in this research project and operate independently of the principal investigators. They have not collaborated or co-published with the principal investigators in the past three years. Each member brings relevant expertise that qualifies them to review the data generated by the study. The IMC will receive one report annually and will provide feedback and recommendations based on their review. Monitoring of study data will occur at multiple levels and frequencies. The Principal Investigator ([name]) will conduct monthly reviews of subject accrual, participant status, data entry quality, adverse events (AEs), and unanticipated problems. [name] will also monitor serious adverse events (SAEs) per occurrence. The IMC will review subject accrual, participant status, and AEs annually, and will also review SAEs per occurrence (if unexpected and related) or annually (if expected or unrelated). Additionally, the National Center for Complementary and Integrative Health (NCCIH) of the National Institutes of Health (USA) will review AEs annually and SAEs per occurrence (if unexpected and related) or annually (if expected or unrelated). The Institutional Review Board will review unanticipated problems according to policy. If the number of overall SAEs exceeds 33% (i.e., 1 in 3) of recruited patients the study will be suspended, and an ad-hoc safety review will be completed. All protocol amendments, except for minor administrative changes, will be submitted prospectively to the NCCIH unless immediate changes are needed to protect participant safety, rights, or welfare. Proposed amendments will first be reviewed and approved by the IMC, and IRB approval will be sought only after approval has been obtained by the NCCIH.

A special provision has been established under the DSMP to address potential mental health crises. The Beck Depression Inventory, administered at all in-person evaluations, includes a question assessing suicidal ideation. Responses to this item will be reviewed immediately. If a participant selects a score of 1, 2, or 3, a predefined protocol will be activated. Participants assessed to be at acute risk will be referred for emergency psychiatric care, either through a hospital emergency department or via 911. Those experiencing significant but non-acute distress will be provided with appropriate clinical resources, including a list of wellness tools, self-care apps, and mental health clinics in New York City that accept various insurance plans (see Supplementary Materials).

All data will be keyed with an anonymous code. All personal information will be treated as confidential; only authorized personnel will have access to this data, and it will not be given to third parties without the subject’s explicit consent. All personally identifiable information will be stored in a secure, encrypted server maintained explicitly for the storage of highly sensitive data, including protected health information. Only the research team will have access to this encrypted data. Experimental results, devoid of any personal information that could identify them, will be maintained in the principal investigator’s files, and eventually released as an open-source database. Results will be reported in peer-reviewed journals. Study completion is expected by Fall 2026.

## Discussion

This paper presents the protocol for a feasibility clinical trial evaluating a remote IML intervention for individuals with chronic stroke. The study includes an objective measure of treatment dose and aims to support mental health recovery in this population. For the feasibility clinical trial, we expect to meet the benchmarks specified in Table 2. In a future efficacy trial informed by this protocol, we expect that participants in the IML group will show improvements in mental health and cognition, accompanied by neuroplastic changes that reflect and support these behavioral gains, compared to the audiobook control group. This hypothesis is grounded in prior research showing that music listening engages multiple brain systems related to the mechanistic pathways (motor, sensory, cognition, and social) through which an enriched environment supports brain plasticity and recovery (Zatorre et al., 2007; Rodriguez-Fornells et al., 2012; Koelsch, 2014; Mas-Herrero et al., 2021; Janata et al., 2002). Importantly, music listening has been shown to activate key brain regions involved in reward, dopaminergic processing, and motivation (Ferreri et al., 2019; Mas-Herrero et al., 2021; Koelsch, 2014). This is particularly relevant given prior research suggesting that the mental health benefits of music are closely linked to reward-related mechanisms (Mas-Herrero et al., 2023). We also hypothesize that improvements in mental health and cognitive functioning will be directly related to the level of treatment dose.

The intervention is guided by the NIH Music-Based Intervention Toolkit (Edwards et al., 2023) and is designed to be low-cost, accessible, scalable, and highly acceptable to patients. Music listening interventions can also optimize the use of sedentary time spent by stroke survivors, as patients can engage in the intervention from home, regardless of motor limitations or access to specialized stroke and/or rehabilitation units (Baylan et al., 2016; Oermann and Riina, 2021). Accurately measuring treatment dose is essential for optimizing rehabilitation outcomes (Schambra et al., 2019). For example, high-intensity, repetitive motor activity is a strong predictor of recovery in stroke rehabilitation (Hatem et al., 2016). An advantage of our approach is our objective quantification of music treatment dose, which has not been quantified in previous IML studies in stroke populations. In the context of IML, dose refers to not only the duration of the music but also to the specific acoustic and musical features of the selected music. These features may differentially impact mental health (Bowling et al., 2023; Orpella et al., 2025). This protocol introduces the use of real-time tracking to objectively measure listening behavior. This approach allows to quantify treatment dose not only by duration but also by analyzing the content of the music. By assessing the relationship between acoustic/musical features and changes in mental health, we can identify which aspects of music may be most therapeutically relevant. This methodology will allow future large-scale, sufficiently powered, clinical trials to assess what amount of IML and which characteristics of the music listened to specifically modulate mental health, cognitive recovery, and brain plasticity.

A strength of this study is access to a large, diverse, and well-characterized population of chronic stroke patients from the greater New York City area. Another strength of the study is the use of multimodal methods to assess intervention effects across behavioral, physiological, and neuroimaging (MRI) domains, providing a more comprehensive understanding of the intervention’s impact. However, the study has limitations. It is not powered to detect clinical changes in mental health, cognition, or neuroplasticity, as its primary goal is to assess feasibility. Additionally, as a single-center study, generalizability to other clinical settings or populations may be limited.Regardless of the outcomes of the proposed work, we believe this study will help advance the field of music-based interventions at the theoretical, experimental, and clinical level. The IML intervention tested here may also be adaptable to other aging-related neurological conditions, such as Alzheimer’s disease and other dementias, broadening its potential public health impact.

## Figures and Tables

**Figure 1. F1:**
[figure not shown]
Clinical trial design.

**Table 1. T1:** Summary of data collected.

	Screening	Baseline Evaluation	Pre-Inter. Period	Pre-Inter. Evaluation	Intervention	Post-inter. Evaluation	Follow-up Evaluation
**Eligibility**							
Hearing Handicap Inventory for the Elderly Screening Version (HHIE-S)	X						
Montreal Cognitive Assessment (MoCA)	X						
Montreal Battery Evaluation of Amusia (MBEA)	X						
Barcelona Music Reward Questionnaire (BMRQ)	X						
MRI Safety Questionnaire	X			X		X	
**Individual Differences**							
Demographics		X					
Musical/Audiobook preferences		X					
Goldsmiths Musical Sophistication Index (Gold-MSI)		X					
**Mental health clinical outcomes**							
Beck Depression Inventory (BDI)		X		X		X	X
Stroke-Specific Quality of Life (SS-QOL)		X		X		X	X
Perceived Stress Scale (PSS)		X		X		X	X
Generalized Anxiety Disorder (GAD-7)		X		X		X	X
Positive and Negative Affect Schedule (PANAS)		X		X		X	X
World Health Organization Well-Being Index (WHO-5)		X		X		X	X
**Cognitive Clinical Outcomes**							
Processing Speed		X		X		X	X
Working Memory		X		X		X	X
Verbal Memory		X		X		X	X
Attention		X		X		X	X
**Biomarkers**							
Structural MRI				X		X	
Functional MRI				X		X	
Physiology				X		X	
**EMAs**							
Motor, sensory, cognitive, and social activity			X		X		
Music activity outside listening session			X		X		
Profile of Mood States (POMS)			X		X		
**Feasibility Measures**							
Burden Ratings (Patients)		X		X		X	X
Acceptability Ratings (Patients)					X		
Feasibility Ratings (Team Member)					X		
Fidelity Ratings (Team Member)					X		

**Table 2. T2:** Outcome measures and benchmarks for success.

Outcome	Description	Benchmark for success
Recruitment	Number of enrolled participants per month	At least 2 per month
Randomization	Proportion of screened patients who are enrolled Proportion of enrolled patients who complete the baseline and pre-intervention evaluations and attend at least one IML/Audiobook session	At least 30% At least 80%
Retention and Adherence	Proportion of enrolled and randomized participants who complete the IML/Audiobook sessions	At least 80% of randomized patients complete at least 80% of the IML/Audiobook sessions
Feasibility	Proportion of listening sessions considered fully feasible; the team member making the phone call will rate the session as “not feasible” , “partially feasible” or “fully feasible”	At least 80% of all sessions considered as fully feasible
Fidelity	Proportion of listening sessions delivered according to the protocol; video calls with patients will be recorded and a team member who was not present during the call will score the session as “delivered according to protocol” or “not delivered according to protocol”	At least 80% of all sessions delivered according to the protocol
Burden	Proportion of planned evaluations that are completed at each time point (baseline, pre-intervention, post-intervention, follow-up) Burden rating: patients will rate each evaluation as “not burdensome” , “partially burdensome” , or “very burdensome”	80% of patients complete the evaluations at each time point At least 80% of patients rate evaluations at each time point as not burdensome
Patient acceptability	Acceptability ratings: patients will rate each listening session as “not acceptable” , “partially acceptable” or “fully acceptable” .	80% of listening sessions rated as fully acceptable

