## Methods and Analysis

### Study Design

We propose a small-sample parallel group randomized controlled feasibility trial where patients will be assigned to an intentional music listening (IML) group (N=30) or to an active control group (N=30) listening to audiobooks (see Figure 1). IML refers to the active practice of listening to music (e.g., paying attention to the music; Dingle et al., 2021). Audiobook listening is a well-established control condition for IML interventions and is recommended by the NIH Music-Based Intervention Toolkit (Edwards et al., 2023; Särkämö et al., 2008; Sihvonen et al., 2020; Baylan et al., 2020). Both groups will complete 1-hour long listening sessions daily for a period of 4 weeks (excluding weekends; 20 sessions total). We will track the music and audiobooks listened to by participants using custom open-source software developed by our team. The study protocol will include a baseline assessment, followed by a pre-intervention period of 4 weeks to assess the stability of outcome measures. Daily control measures will be collected during the pre-intervention period using ecological momentary assessments (EMAs). After the 4-week pre-intervention period, a pre-intervention evaluation session will be completed. The intervention will then start. As in the pre-intervention period, daily control measures will continue to be collected during the intervention using EMAs. After the 4-week intervention period, a post-intervention assessment will be conducted, with a follow-up at 3 months. Baseline, pre-, and post-intervention evaluations will include clinical outcomes (i.e., behavioral tests of mental health and cognition). Pre- and post-intervention evaluations will include biomarkers (i.e., structural and functional MRI and physiology) in addition to clinical outcomes. The follow-up session will only include clinical outcomes. Table 1 provides an overview of all measures collected throughout the study and the time points at which they are administered.

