### Study population

We aim to enroll 60 participants (30 per group), aged 50 to 90, with a confirmed diagnosis of ischemic or hemorrhagic stroke occurring at least six months prior to enrollment. The sample size was informed by previous feasibility studies of complementary health interventions (Richard-Lalonde et al., 2023; Doorley et al., 2022; Portz et al., 2023; Smith et al., 2022). Participants will be excluded if they meet any of the following criteria: (1) significant hearing loss, defined by a score >26 on the Hearing Handicap Inventory for the Elderly Screening (HHIE-S; Ventry and Weinstein, 1982); (2) contraindications for MRI; (3) cognitive impairment that may interfere with completion of study procedures, defined as a Montreal Cognitive Assessment (MoCA; Nasreddine et al., 2005) score below 22 (unless the lower score is attributable to expressive aphasia); (4) specific musical anhedonia, defined as a score below 60 on the Barcelona Music Reward Questionnaire (BMRQ; Mas-Herrero et al., 2013); or (5) amusia, defined as a score below 70% on the Montreal Battery of Evaluation of Amusia (MBEA; Peretz et al., 2003). Participants will not be excluded if they are currently taking medications that may affect brain function (e.g., antidepressants) or if they are engaged in other complementary therapies (e.g., mindfulness, yoga). However, they will be instructed not to initiate any new medications or therapies during the study period. Participants who begin a new treatment during the study will be excluded from the analysis. Participants will also be discontinued from the study upon their request or if there is a worsening of their medical condition that compromises safety or study participation.

Eligible patients will be contacted by phone, and the study will be explained using a standardized script. Patients who do not make an immediate decision (e.g., need time to consider participation) will receive up to two follow-up contacts via phone or email over a two-week period. To meet recruitment targets, we aim to enroll at least five participants per month over the course of 12 months.

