Each daily remote listening session will begin with a team member calling the patient on the iPad at a pre-arranged time. At the beginning of the session, the playlist will be updated according to the patient’s preferences and mood. Patients will then be asked to listen intentionally to the playlist without engaging in other activities (e.g., doing chores). However, participants will be allowed to engage in music-related behaviors during listening, such as singing or moving to the music. The total duration of each session will be one hour, including at least 40 minutes of music listening and up to 20 minutes for setup, preparation, and playlist updates. Team members will remotely monitor the listening sessions and will be available via FaceTime throughout the session to provide support if needed. This will improve adherence to the protocol. To accommodate varying levels of impairment, needs, and technological familiarity, team members will provide as much support as each participant requires, while also encouraging patient agency. Participants will be guided as needed but allowed to manage their listening sessions independently (e.g., by skipping songs on their own). Listening sessions will also be video-recorded to allow for later annotation of music-related behaviors (e.g., dancing). If video monitoring or recording fails due to technical issues, the research team will first attempt to resolve the problem remotely via FaceTime. If the issue cannot be resolved remotely, a team member will visit the participant in person to fix the problem or replace the iPad. If feasible, a make-up session will be conducted on the same day. At the end of each session, the monitoring team member will rate the feasibility of the session (“not feasible” , “partially feasible” or “fully feasible”) and the participant will rate the acceptability of the session (“not acceptable” , “partially acceptable” or “fully acceptable”). Finally, a team member who was not involved in the listening session will review the session’s video recording and score its fidelity as either “delivered according to protocol” or “not delivered according to protocol.”

The same control measures collected during the pre-intervention period will continue to be gathered during the intervention using EMAs via the mEMA app (motor, sensory, cognitive, and social activity; music engagement outside of scheduled sessions; and the POMS).

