### Statistical analysis

The primary and secondary outcomes of intervention feasibility will be reported using percentages (see Table 2, benchmarks for success). One-sided exact binomial tests and proportional z-tests will be used to assess whether the outcomes have success rates above the benchmarks. Success rates will be compared between the treatment group and control group using Chi-squared tests or Fisher’s Exact Tests if non-normality presents. We will identify potential factors that are associated with the feasibility outcomes, which will help refine the design of a large-scale clinical trial.

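### Three primary outcomes count sessions, up to 20 per participant, but the named tests assume independent observations, so error rates are inflated by an amount that depends on an unstated within-participant correlation

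*Protocol article*

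**What the plan says.** The Outcome measures section lists feasibility, fidelity and acceptability among the primary outcomes. Table 2 gives each of them a session denominator and an 80% benchmark:

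- Feasibility: "At least 80% of all sessions considered as fully feasible".
- Fidelity: "At least 80% of all sessions delivered according to the protocol".
- Acceptability: "80% of listening sessions rated as fully acceptable".

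Study population sets the target: "We aim to enroll 60 participants (30 per group" in the planned design. Study Design gives the schedule in each arm: "excluding weekends; 20 sessions total". The ratings repeat within a person. The intervention section says: "At the end of each session, the monitoring team member will rate the feasibility of the session". The participant rates acceptability at the same moment, and fidelity is scored later from the recording of each session.

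The Statistical analysis section covers all primary and secondary feasibility outcomes together. It reports percentages, tests them against the benchmarks with one-sided exact binomial tests and z-tests for proportions, and then adds: "Success rates will be compared between the treatment group and control group using Chi-squared tests", with Fisher's exact test as the alternative. It mentions no clustering, participant-level summary or robust variance, and it does not treat session-level outcomes differently from patient-level ones.

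**The concern.** Binomial, z, chi-squared and Fisher tests all take each observation as independent. Here up to 20 observations come from one person, with the same impairment, the same familiarity with the technology and the same taste in self-selected content. Some participants will find nearly every session acceptable, and others will find few acceptable. Staff will find some participants easy to run and others hard. Sessions from one person therefore carry less information than the same number from different people, and the named tests understate the standard error.

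At stake is the inferential part of the feasibility conclusion. A few consistently favourable participants could push a session-level outcome significantly above its benchmark. A few consistent participants who happen to fall in one arm could make the arms look different. The trial exists to inform the design of larger trials, so a spurious difference in acceptability between music and audiobooks could mislead the choice or handling of the control condition.

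**Working it through.** **Inputs from the protocol article.** 60 participants, 30 per arm (Study population). m = 20 planned sessions each (Study Design). Benchmark p0 = 0.80 on sessions (Table 2). One-sided benchmark tests and chi-squared or Fisher tests between arms (Statistical analysis).

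**Assumptions, because the document gives no value.** Alpha is 0.05, one-sided against the benchmark and two-sided between arms. ICC ranges from 0.01 to 0.3. All 20 sessions are held. The plan states no error rate or power, so there is no figure of its own to reproduce.

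**Step 1: the named test under independence.** n = 60 × 20 = 1,200. The exact binomial test at one-sided 0.05 declares success from 984 sessions (984/1,200 = 82.0%). Its actual error is 4.4%, so it is valid if sessions are independent.

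**Step 2: design effect.** DE = 1 + (m − 1) × ICC = 1 + 19 × ICC. Effective sample size = 1,200/DE. Standard error at 80% = √(0.16/1,200 × DE).

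| ICC | DE | Effective sessions | SE (percentage points) |
|---|---|---|---|
| 0 | 1.00 | 1,200 | 1.15 |
| 0.01 | 1.19 | 1,008 | 1.26 |
| 0.05 | 1.95 | 615 | 1.61 |
| 0.1 | 2.90 | 414 | 1.97 |
| 0.2 | 4.80 | 250 | 2.53 |
| 0.3 | 6.70 | 179 | 2.99 |

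**Step 3: true error of the named tests.** The approximations are 1 − Φ(1.645/√DE) for the benchmark and 2 × [1 − Φ(1.96/√DE)] between arms. Example at ICC 0.2: √4.8 = 2.19; 1.645/2.19 = 0.75, giving 22.6%; 1.96/2.19 = 0.89, giving 37.1%. Beta-binomial simulation (100,000 trials, true rate exactly 80%, tests applied to pooled sessions) agrees closely:

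| ICC | Benchmark, formula | Benchmark, simulated (exact test) | Between arms, formula | Between arms, simulated |
|---|---|---|---|---|
| 0.01 | 6.6% | 5.8% | 7.2% | 7.2% |
| 0.05 | 11.9% | 11.2% | 16.0% | 16.2% |
| 0.1 | 16.7% | 15.8% | 25.0% | 25.0% |
| 0.2 | 22.6% | 22.3% | 37.1% | 37.2% |
| 0.3 | 26.3% | 26.4% | 44.9% | 45.2% |

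The formula for the benchmark runs slightly high at low ICC because the exact test starts from 4.4% rather than 5%.

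**Step 4: fewer sessions.** With 16 sessions each, the exact benchmark test has an error of 10.4% at ICC 0.05 and 20.9% at ICC 0.2, so some missed sessions do not remove the problem.

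**Step 5: programmes that really miss the benchmark.** With the same cut-off of 984, a true rate of 75% passes in about 0.02–0.03%, 0.4% and 1.2–1.3% of trials at ICC 0.1, 0.2 and 0.3. A true rate of 78% passes in about 2.4%, 6.2–6.3% and 9.6%.

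**Step 6: does respecting the participant repair it?** A t-test on participants' session proportions, in the same simulations and over ICC 0.01 to 0.5, gives 5.6% to 7.5% against the benchmark (the small excess comes from skew) and about 5% between arms. With equal session counts the mean of those proportions equals the pooled proportion, so the estimate does not change.

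**The case against.** The other side has five fair points.

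- **Size.** A reader might infer that error rates will be several times nominal. The document does not support that without conditions, because it gives neither the ICC nor alpha. At ICC 0.01 the errors are about 6% and 7%, little above 5%. At 0.05 the benchmark test is at roughly twice nominal. Only from about 0.1 upward does several times describe both tests. This stands, and the size must be read as a range.
- **Consequence for the benchmark.** The inflated error is computed at a true rate of exactly 80%, which meets Table 2's own wording. A reader might infer that clearly inadequate delivery could be certified. Step 5 shows otherwise: a programme 5 points short almost never passes, and only narrow misses with high ICC remain exposed. This stands for the benchmark test. It does not answer the inflation of the arm comparison.
- **Description comes first.** Outcomes are reported as percentages, clustering does not bias them, and Table 2 is worded on the percentage rather than on a p-value. This limits the damage, but the tests are still planned and would still be reported.
- **A separate analysis plan may handle it.** It may. The protocol never says in words that sessions are treated as independent; this follows from the tests it names. The finding therefore concerns those named tests, which an analysis plan that followed the protocol would inherit.
- **Source of the correlation.** A reader might add that the same staff member runs and rates a participant's sessions. The document does not say how staff are assigned, and fidelity is scored by someone not involved in the session. Nothing here depends on that.

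**Conclusion.** The point holds and is wrong as written for three primary outcomes: the denominators are sessions, the sessions are repeated within participants, and every named test requires independence. The direction is close to certain, because positive within-participant correlation makes the tests anti-conservative. The size is conditional. At alpha 0.05 with 20 sessions each and ICC from 0.01 to 0.3, the benchmark test's error runs from about 6% to 26% and the arm comparison's from about 7% to 45%. The arm comparison is the more exposed of the two.

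The limits are equally clear. The percentages themselves are sound, and delivery well below 80% would rarely pass. Retention and adherence and both burden benchmarks count patients, so the concern does not reach them. The document does not support a reading that the feasibility conclusions as a whole are unreliable.

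**What to change.** In the Statistical analysis section, treat the three session-level outcomes separately:

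1. Keep the Table 2 proportion of all sessions as the estimate.
2. Base the benchmark test, the confidence interval and the arm comparison on variance clustered by participant. Use either a logistic GEE with independence working correlation and robust standard errors (arm as covariate for the comparison), or a bootstrap that resamples whole participants.
3. Keep exact binomial and Fisher tests for the patient-level outcomes only.
4. State alpha and sidedness, and report the observed ICC, which the larger trial will need.

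The unweighted mean of participants' proportions should not replace the estimate without comment. When session counts differ through dropout or missed sessions, it weights people rather than sessions and so answers a different question from Table 2.

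The cost is a few sentences and a few lines of code, with no change to design, sample size or data collection. Intervals widen: with a design-effect-adjusted z-test, the observed rate needed to show success rises from about 82% to 82.7% at ICC 0.05 (0.80 + 1.645 × 0.0161) and to 84.2% at ICC 0.2 (0.80 + 1.645 × 0.0253). If nearly all sessions succeed, which is plausible for fidelity, GEE and bootstrap intervals can break down, so a fallback for results near 100% should be specified in advance.
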